# Introduction

One in eight cancers diagnosed worldwide in 2020 were breast cancers (BCs); likewise, one in four of all new cancer cases in women are BCs (Global Cancer Observatory [GLOBOCAN], 2020). Globally, female BC surpassed lung cancer in 2020 to become the most commonly diagnosed cancer, affecting 2.1 million women each year with new cases expected to increase by 46.5% in the year 2040 (GLOBOCAN 2020; World Health Organization [WHO], 2019). In African countries, BC is the most frequent cause of cancer mortality causing one in five deaths in African women (Vanderpuye et al., 2017). In Nigeria, BC was the most common cancer recorded in the year 2018, accounting for 22.7% of all cancer cases and responsible for 16.4% of all cancer deaths (WHO, 2020). While the mortality from BC in a developed country like America is 19%, that of Nigeria is triple (Federal Ministry of Health, 2018).

Several treatment modalities exist for BC, which include chemotherapy, targeted therapy, surgery, and hormone therapy (Diaby et al., 2015; Matsen & Neumayer, 2013). Also, various side effects have been found to be specific for the various treatment modalities which make the BC treatment highly challenging. Focusing on women receiving BC chemotherapy is important as the usage of chemotherapy in treating women with BC is universal (Fan et al., 2014; Gold et al., 2014), cutting across all stages of BC (Du & Goodwin, 2001), and used before and after surgery (Charfare et al., 2005). As various side effects have been reported for the various treatment modalities (Lo et al., 2017); also, symptom clusters of pain, fatigue, anxiety, and depression have been documented among women receiving BC chemotherapy (Browall et al., 2017; So et al.,2009).

It has been estimated that 30-50% of women diagnosed with BC have psychological concerns somewhere along their illness trajectory (Gupta et al., 2020; Hewitt et al., 2004). Psychological concerns have been reported as one of the most common adverse effects experienced by BC women receiving chemotherapy (Henderson et al., 2012). Common psychological concerns reported include symptom burden, symptom distress, fear, anxiety, depression, deteriorated quality of life, poor social support, and unmet supportive care needs (Au et al., 2012; Hewitt et al., 2004; Browall et al., 2017). Furthermore, self-efficacy in coping, which refers to an individual’s belief in her capacity to cope effectively with or adjust to a particular situation (Bandura, 1977; Chesney et al., 2006), has been reported to reduce significantly in this population (Akin et al., 2008). Furthermore, evidence has shown that assessing self-efficacy in coping in cancer patients could facilitate identifying coping strengths that need to be reinforced or coping weaknesses that need to be modified through appropriate interventions with a bid to minimising the psychological burden of cancer (Heitzmann et al., 2001). Enhancing coping with chemotherapy among BC patients is important as this can help improve emotional state of these women and encourage them to adhere to the treatment (Watkins et al., 2017).

Although psychological concerns are common in this population; they are not inevitable (Guo et al., 2013), as appropriate interventions can be targeted towards mitigating the psychological concerns. Similarly, the transactional model of stress and coping has demonstrated that after a stressful condition, an individual would assess his/her available coping resources and adopt coping strategies to cope with the situation (Glanz et al., 2002).

To address psychological concerns of women diagnosed with BC, some interventions have been suggested. Guarino et al. (2020) conducted a systematic review on interventions for addressing psychological concerns of women diagnosed with BC and identified three major categories of such kind of interventions, including cognitive-behavioural interventions, psychoeducational interventions (PEI), and supportive-expressive interventions (SEIs). A medium effect size was found for PEIs and SEIs on improving anxiety, depression, mood, and quality of life. As educational needs have also been reported in this population, PEIs are important in addressing the psychological and educational concerns (Au et al., 2012; Fanakidou et al., 2017). PEIs have been defined as a broad range of activities that combine structured transfer of knowledge through education with psychological activities like counselling and supportive interventions (Oncology Nursing Society, 2021).

While the need to provide PEIs for BC women has been documented in literature; mHealth, defined as “health-related services delivered through mobile communication devices” (Whitaker 2012) has been suggested as a medium to deliver these interventions because mobile phones have become ubiquitous (Mobasheri et al., 2014). Similarly, Okunade and colleagues (2020) also noted that one of the developments after the COVID-19 pandemic in Nigeria would be the integration of telemedicine into the care of oncology patients; however, evidence to guide this integration is still being gathered and not yet established.

Although the benefits of mHealth interventions have been reported along the BC illness trajectory (Beauchamp et al., 2020; Galiano-Castillo et al., 2017; Jongerius et al., 2019), mHealth interventions used specifically in women receiving BC chemotherapy is unclear and the effect of these interventions on psychological concerns in this population is inconsistent. Similarly, as the usage of mHealth in this population is relatively new and with very limited evidence, this study, which to the best of our knowledge is the first in Nigeria, will generate evidence for integrating mHealth into care for women with BC receiving chemotherapy. Similarly, nurses will be informed of the effectiveness of a mHealth psychoeducational intervention (mPEI) for this population. It is hoped that the psychological and educational concerns of Nigerian women with BC will be adequately addressed while receiving chemotherapy.

**Aim and Objectives**

The study aims to develop and implement a culturally adapted mPEI for BC women receiving chemotherapy in Nigeria. The objectives of the study are to: 1) evaluate the effectiveness of the programme on self-efficacy (primary outcome), coping, symptom distress, anxiety, depression, and quality of life (secondary outcomes) among women with BC receiving chemotherapy; and 2) explore the participants’ experiences and feelings towards the intervention.

**Hypothesis**

It is hypothesised that participants who receive the mPEI, when compared with the control group at baseline and immediately after the intervention, will demonstrate significantly higher level of self-efficacy, coping, quality of life, and significantly lower level of symptom distress, anxiety and depression.

**Development of the Intervention**

The development of the mPEI is guided by evidence from the systematic review, a qualitative study conducted by the research team and a theoretical framework.

A systematic review was conducted by the research team featuring seven mHealth interventions used among 799 women with BC undergoing chemotherapy. The study showed that most of the interventions were application-based and focused on psychoeducation. The major components of the interventions were education, group interaction, self-reporting of symptoms and expert consultation, and most of the intervention providers were nurses. The meta-analysis results indicated a significant improvement in the quality of life (standardised mean difference [SMD] = 0.32, 95% confidence interval [CI] [0.07, 0.58], p = .01, I2 = 17%). No significant effects were found for anxiety (SMD = 0.00, 95% CI [-0.32, 0.32], p = 1.00, I^2^ = 64%] and depression (SMD = 0.02, 95% CI [-0.17, 0.20], p = .87, I^2^ = 0%). Similarly, results from previous studies also found conflicting results. However, two of the studies included in this systematic review (Hou et al.,2020; Zhu et al 2018) suggest that further rigorous trials should be conducted to confirm the effect of mHealth interventions on these outcomes, hence, both outcomes will be measured in this study.

Individual studies suggest reduced symptom prevalence (p = .033, d =.27), symptom distress (p = .004, d = .004), symptom interference (p = .02, d = .51), supportive care needs (p < .05, d = 2.43); improved self-efficacy (p = .03, d = 0.53) and emotional functioning (p = .008, d = .30). The methodological quality of the included studies ranged from low to moderate. The study concluded that mHealth interventions might be helpful in addressing certain psychological issues experienced by women receiving chemotherapy for BC, although the evidence is still being gathered and not yet conclusive.

In order to identify the psychological and educational needs of Nigerian women receiving chemotherapy so as to develop culturally-adapted interventions, as well as to identify the perceptions on this kind of intervention, a qualitative study was conducted by the research team. A total of 32 women who had completed BC chemotherapy were recruited from two tertiary hospitals in Nigeria- Lagos State University Teaching Hospital and Lagos University Teaching Hospital. Focus group interviews were conducted and is was found that the participants perceived the proposed intervention to be feasible. The participants suggested contents for the proposed mHealth intervention. The contents include information on chemotherapy, how to deal with fear of chemotherapy, nutritious diet locally available and information on exercise. Many of the participants found the first cycle of chemotherapy extremely challenging. Psychological disturbances experienced include sadness, fear of chemotherapy, confusion, insomnia. Their needs were majorly psychological and informational. Coping resources available for the participants were support from their families, health professionals, BC survivors and their affiliated churches. Coping strategies adopted include being positive, prayer, online information, and exercise.

Regarding the theoretical framework underpinning the intervention, the self-efficacy theory was adopted to guide its development. Evidence suggests that people’s belief in their ability to handle or cope with a threat can lower their anxiety and depression as an association has been found between low self-efficacy and stress, anxiety and depression (Bandura 1995; Zulkosky, 2009). Similary, Borjalilu et al. (2017) identified an association between high self-efficacy in coping and improved quality of life among women with BC. They also reported that women with BC who had lower self-efficacy had more physical symptoms including nausea, pain, numbness, weakness, swollen hands, legs and feet.

Four constructs from the self-efficacy theory underpin this intervention. They include performance accomplishment, vicarious experiences, verbal persuasion, and emotional arousal. *‘Vicarious experiences’* refers to the motivation gained on observing people successfully completing a task (Bandura, 1997). *‘Verbal Persuasion’* refers to the encouragement gotten from receiving a verbal feedback while undergoing a complex task (Bandura 1997). *‘Emotional arousal’* refers to the emotional responses that are triggered by stressful circumstances. High emotional arousal in people usually hamper performance as fear generated by stressful situations can culminate in elevated levels of anxiety which reduces self-efficacy (Bandura, 1977). However, if the fear of the individual can be controlled, the likelihood of success is increased (Wallace & Kernozek, 2017). ‘*Performance accomplishment’* refers to experiences gained when a new challenge is accomplished successfully. Occasional failures are overcome easily after repeated success. With the implementation of the mPEI programme, self-efficacy in coping with demands of chemotherapy will be increased. With enhanced self-efficacy, there will be a reduction in anxiety, depression and symptom distress which will culminate in an improved quality of life. Evidence suggests that with the usage of a mPEI among women with BC, psychological benefits such as reduced anxiety, depression, symptom distress and improved quality of life are obtained (Fjell et al., 2020; Ghanbari et al., 2021; Lepore et al., 2014; Zhu et al., 2018).

A conceptual framework showing the relationship between the mHealth programme components and the outcomes is presented in Appendix A.

**Design of the mPEI programme**

A mobile application will be used to deliver the mPEI programme. The formulation of the app was developed by *Deltree Technologies,* an Information and Communication Technology (ICT) company based in Nigeria. Based on the self-efficacy theory, findings from the systematic review, and consultation with experts in BC management and psychoeducation, the mPEI programme contains five components: BC education, coping skills training, discussion forum, nurse-led consultation, and psychological support. The design of the intervention is presented in Appendix B.

***Components and contents***

- *BC education*

As found in studies in the systematic review (Hou et al., 2020; Zhu et al., 2018), the education component provides information on BC, chemotherapy side effects, and how to cope with chemotherapy. The education component is also guided by findings from an extensive literature review, consultation with professionals in oncology, findings from the phase II qualitative study, knowledge gained from a training the principal investigator received on psychoeducation, and based on the clinical practice guidelines developed by the National Cancer Control Initiative (National Breast Cancer, 2003). BC education will feature through the six weeks of the intervention.

BC education in the mPEI programme addresses the ‘performance accomplishment’ construct in the self-efficacy theory. As the participants are exposed to BC education and they successfully implement the lessons learnt; this will bring a feeling of performance accomplishment which will improve their self-efficacy to cope with the demands of the chemotherapy experience.

The BC education is delivered on the app in three formats namely, text with pictures, audio and video format. The language will be in English which is the official language in Nigeria. The participants will be expected to read and/or watch the BC education content within the week of posting.

As the previous qualitative study suggested, stories from BC survivors are incorporated into the educational platform in a video format for 15 minutes per week for the first, third and fifth weeks.

- *Coping skills training*

This component provides training on coping skills as evidence has shown that improving knowledge about coping resources, strategies and skills can culminate in positive appraisal while improving self-efficacy in coping with treatment (Bandura, 1977; Swanson et al., 1999; Watkins et al., 2017). There are three sessions of coping skills training. This is to cover three of the six weeks. The sessions focus on coping with chemotherapy side effects, maximising coping resources, dealing with psychological issues through religion and spirituality, maximising coping strategies and leveraging on family support.

This component addresses the ‘performance accomplishment’ construct of the self-efficacy theory. As the participants are taught coping skills, and they successfully implement these skills; this will bring a feeling of ‘performance accomplishment’, which will improve their self-efficacy to cope with the demands of the chemotherapy experience. Similarly, as the participants learn coping skills based on positive re-interpretation, acceptance, and spirituality, a positive emotion will be induced which will improve their coping with the chemotherapy experience. The participants will be expected to read and/or watch the coping skills training content within the week of posting.

- *Discussion forum*

As found in the systematic review (Hou et al., 2020; Lepore et al., 2014; Zhu et al., 2018), the discussion forum will feature discussion topics from the education, and this will be divided into sessions of six weeks and moderated by the researcher. Discussion forum in the mPEI programme will address the ‘vicarious experiences’ construct in the self-efficacy theory. As the women interact on the platform and share their success stories in adjusting and coping with the chemotherapy experience, this will encourage others and they will be motivated to complete the task which is successfully completing the chemotherapy.

The discussion forum will be implemented real time and non-real time. The real-time discussion will be at a time agreed on by the participants. Those that are not online at that time can leave further comments on various issues raised at their convenient time. The participants will be free to use a name they are comfortable with so their identity can be confidential. Similarly, they will not be required to display their pictures to maintain privacy. There will be six discussion groups in all with each group containing an average of 10 members as evidence suggests that this number allows for meaningful interaction and group administration (Biggs et al., 2020). The discussion forum will feature through the six weeks of the intervention.

- *Nurse-led consultation*

This will provide a means of answering questions and supporting participants in terms of their informational and psychological needs. This function will be provided by the oncology nurse designated for each participant through a 15-20-minute call in the first week, third week and fifth week.

This component will address the ‘verbal persuasion’ construct of the self-efficacy theory. As the participants consult the nurses, they will receive verbal encouraging feedbacks that will support them through the chemotherapy experience.

- *Psychological Support*

The psychological challenge experienced by women receiving breast cancer chemotherapy varies depending on her temperament, her other burdens, and psychological history (Greenberg, 2010). Psychological support will be provided by actively listening to the participants, provision of a means to verbalize worries and concerns, and providing informational support. The psychological support will be given on an individual basis through the nurse-consultation function. This will entail 15-20 minutes call first week, third week and fifth week by oncology nurses from the research team.

This component will address the ‘emotional arousal’ construct of the self-efficacy theory. The fear of cancer and the chemotherapy experience will be controlled through the psychological support. As fear is controlled, anxiety will be reduced and self-efficacy to cope with the chemotherapy experience will increase.

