***Intervention format***

PEIs can be delivered through various formats, including individual, group, home, hospital, or community-based (Moore et al., 2021; Sin & Norman, 2013). For this study, as evidence from the systematic review conducted suggested that PEIs delivered through the mobile phone might be beneficial in resolving certain psychological issues in this population; the intervention will be delivered through a mobile phone. Similarly, as the intervention is multi-component, a combination of individual and group formats will be employed. The BC education, coping skills training and discussion components will be delivered on a group basis; psychological support and nurse-led consultation will be delivered on an individual basis. Furthermore, the intervention will be community-based as chemotherapy in Nigeria is delivered on an out-patient basis.

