***Sample size planning***

Sample size is calculated based on the primary outcome of self-efficacy. Power analysis was done with G*Power version 3.1 (Faul et al., 2007), and a medium effect size of 0.53 which was demonstrated in a previous mHealth psychoeducational study featuring women undergoing BC chemotherapy. Power was 0.8 and *p*<.05 with 10% attrition which was an average attrition rate found from a recent mhealth systematic review conducted on this population (Cohen 1988; Zhu et al., 2018). Sample size is estimated to be 126 participants, but the exact number will be confirmed after the pilot study.

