**Data analysis**

SPSS version 25 will be used to analyse quantitative data. The demographic data and clinical data will be analysed through descriptive statistics including frequencies, percentages, mean and standard deviation. Continuous variables at baseline, and immediately after the intervention will be compared through independent samples t- test for the continuous variables and chi-square or Fisher’s exact test for the categorical variables where appropriate. Primary and secondary outcomes data will be analysed through the generalized estimating equation (GEE) model provided the assumptions for homogeneity of variance and normality are met (Bell et al., 2014). In a bid to control for attrition bias, the intention-to-treat principle will be used to account for loss to follow up (Nam & Toneatto, 2016).

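### The sample size makes no allowance for clustering by discussion group in the intervention arm, and the analysis names no group level, so the stated 80% power holds only if the within-group correlation is zero

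*Protocol*

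**What the plan says.** **Group delivery.** Under Components and contents (Discussion forum): "There will be six discussion groups in all with each group containing an average of 10 members". Under Intervention format: "The BC education, coping skills training and discussion components will be delivered on a group basis". The same forum text gives peer influence as the intended mechanism: women sharing their successes are meant to motivate others, which the Protocol ties to the vicarious-experience construct of self-efficacy theory. Self-efficacy is the primary outcome. The Control Group section describes standard care only, with no groups. Randomisation is of individual women, 1:1.

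**Sample size.** Under Sample size planning (main RCT): "Sample size is calculated based on the primary outcome of self-efficacy", with "a medium effect size of 0.53 which was demonstrated in a previous mHealth psychoeducational study". The remaining inputs are "Power was 0.8 and *p*<.05" and "with 10% attrition which was an average attrition rate found from a recent mhealth systematic review". The result is "Sample size is estimated to be 126 participants, but the exact number will be confirmed after the pilot study". The section gives no ICC, design effect or number of groups.

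**Analysis.** Under Data analysis (main RCT), continuous variables are compared between arms by independent-samples t-test at baseline and after the intervention. For the trial outcomes: "Primary and secondary outcomes data will be analysed through the generalized estimating equation (GEE) model". The section does not say what the GEE clusters on, which working correlation it uses or how its variance is estimated. It does not mention discussion group.

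**The concern.** This is a partially nested design: outcomes may be correlated within discussion groups in one arm, while women in the other arm are independent. A positive within-group correlation makes the intervention mean less precise than 57 independent women would make it.

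Two things are at stake. First, the stated power rests on an unstated assumption of zero correlation, although the programme is built so that group members influence one another. Second, an analysis that ignores the groups would give standard errors that are too small and intervals that are too narrow, so that an effect is declared too readily. The second problem cannot be repaired afterwards if nobody recorded which woman was in which group.

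**Working it through.** **Inputs from the Protocol:** d = 0.53 (SD taken as 1), power 0.80, alpha 0.05, attrition 10%, 1:1 allocation, N = 126 (63 per arm), six groups in the intervention arm. **Assumptions:** a two-sided test (sidedness is not stated), and an ICC of 0.01 to 0.10 (none is given).

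**1. Reproduce 126.** A two-sample t-test with these inputs needs 57 per arm, 114 in total; 114 × 1.1 = 125.4, which rounds up to 126. Power at 57 per arm is 80.1%, so there is almost no slack. The normal approximation gives 56 per arm; 56/0.9 = 62.2, rounded up to 63 per arm, is again 126. Both routes assume independent observations. A one-sided test needs only 45 per arm (100 in total after attrition) and does not reproduce the figure.

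**2. Add clustering in one arm.** With n = 57 per arm and m = 57/6 = 9.5:

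- v1 = [1 + (m − 1) × ICC]/57 for the intervention arm, v2 = 1/57 for control, SE = √(v1 + v2)
- normal-approximation power = Φ(0.53/SE − 1.96)
- Satterthwaite df = (v1 + v2)² / [v1²/5 + v2²/56], with power from the non-central t with non-centrality 0.53/SE
- true error of a test that ignores groups = 2 × [1 − Φ(1.96 × SE at ICC 0 / SE)]

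At ICC 0.05: v1 = 1.425/57 = 0.0250, v2 = 0.0175, SE = 0.206. Then 0.53/0.206 = 2.57, and Φ(2.57 − 1.96) = 73%. The df are 13.9, which gives 67%. The SE ratio is 1.10, and 2 × [1 − Φ(1.96/1.10)] = 7.5%.

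| ICC | Variance of difference | Power, normal | Power, Satterthwaite | True error if groups ignored |
|---|---|---|---|---|
| 0 | reference | 80.8% | 76% | 5% |
| 0.01 | +4.25% | 79.1% | 74% | 5.5% |
| 0.02 | +8.5% | 77.5% | 72% | 6.0% |
| 0.05 | +21% | 72.9% | 67% | 7.5% |
| 0.10 | +42.5% | 65.9% | 58% | 10% |

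The Satterthwaite column is already at 76% when the ICC is zero. That part of the drop is the price of estimating a between-group variance from six groups; the rest is due to the clustering.

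**3. What baseline adjustment recovers.** Assume a baseline correlation of 0.5, which the documents do not give. The factor 1 − 0.5² = 0.75 multiplies the variance. At ICC 0.05, SE = √[0.75 × (1.425 + 1)/57] = 0.179. This gives 84% by the normal approximation but about 79% with 13.9 Satterthwaite df. If group effects arise only after baseline, adjustment cannot remove them: SE = √[(0.75 + 8.5 × 0.05 + 0.75)/57] = 0.184, with 82% and 76% respectively.

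**The case against.** **The GEE may handle this.** A reader might infer that the GEE treats all women as independent. The Protocol does not say so: it is silent on the cluster unit, which may be fixed in a statistical analysis plan that is not at hand. Only the t-test is explicitly an independence analysis, and the primary and secondary outcomes are assigned to the GEE. This objection stands, so standard errors that are too small are a conditional risk and not an established error. It does not reach the sample size, which the Protocol itself fixes without any allowance.

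**The ICC may be small.** Education and coping content is delivered through the app for each woman to read or watch, the principal investigator delivers every session and moderates every forum, the forum runs 30 minutes a week and partly outside real time, and nurse calls are individual. All this argues for a low value, and at 0.01 the normal-approximation loss is under two points. A reader might infer that the trial is certainly underpowered; without an ICC, that cannot be said. But a single moderator removes differences between moderators, not peer influence, which is an intended mechanism.

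**Type I error inflation needs a condition.** If the programme affects nobody, individually randomised women acquire no group correlation and the error stays near 5%. The inflated figures apply where groups move outcomes up or down while the average effect is zero. This stands.

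**N is provisional.** It is to be confirmed after the pilot. But the pilot has 15 intervention women (one or two groups at the planned size), no ICC among its objectives and only descriptive quantitative analysis, so it cannot supply the missing value.

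**Baseline adjustment might seem to restore full power.** The 84% at ICC 0.05 is a normal approximation; under the small-sample degrees of freedom that six groups call for, it is about 79% or less.

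**Conclusion.** The point holds in conditional form. The design has six interacting groups in one arm and none in the other, and 126 contains no allowance for this. The 80% is correct only at zero ICC in an analysis that treats women as independent. Over an assumed ICC of 0.01 to 0.10, power runs from about 79% down to 66% by the normal approximation, or from 74% to 58% with Satterthwaite degrees of freedom. The loss is minor at the low end and material from about 0.05.

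The figures rest on 57 analysed per arm, six equal groups of 9.5, equal total variance in both arms and a two-sided test. The documents do not establish that the GEE ignores the groups or that power certainly fails.

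**What to change.** 1. In Sample size planning, state power as conditional on an assumed ICC range when N is confirmed after the pilot, using the partially nested variance above.
2. Record each intervention woman's discussion group in the trial data set from the start of delivery.
3. Analyse the primary outcome with a partially nested mixed model: a random discussion-group effect in the intervention arm only, controls as singletons, and Satterthwaite or Kenward-Roger degrees of freedom. This replaces the independence t-test for the outcome comparison. Do not rely on an uncorrected sandwich variance with six clusters.
4. Adjust for baseline CBI-B, which is already collected. Describe the gain as partial.

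The cost is Protocol or analysis-plan wording and one extra variable, with no extra patients. The downside is a less favourable stated power and somewhat wider confidence intervals.
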